### Enjoyment and engagement—facial expression analysis

Individual video footage of a given child participating in the Flavour Explorers activity will be annotated continuously with an assessment of current facial expression. Coders assign an *affect valence* measure to the current facial expression, from − 2 (very negative) to + 2 (very positive), where 0 is neutral, updated upon changes of valence, such that a given valence measure is a time series covering the duration of that child’s Flavour Explorers session-time. See Additional file 1: Appendix 2 for more details on the coding regime. This valence time series is used to derive two measurements of behaviour which we term *Enjoyment* and *Engagement*, as defined below.*Enjoyment*: a quantitative measure of child's facial expression valence on average over one ‘Flavour Explorers’ data collection session. Calculated as mean valence over all timesteps.*Engagement*: a quantitative measure of amount of *change* in facial expression valence. To calculate this measure, we take the first derivative of valence and calculate its mean absolute value over the number of timesteps in the video recording.

### Why use these two measures?

Engaging in the tasting activity can produce strong negative-valence facial expressions, for example nervousness/fear on approaching an unfamiliar food, or when tasting sour or disliked foods. A child who mostly maintains a neutral face throughout could have a similar Enjoyment (mean valence) score as a child who swings between episodes of strongly positive and negative expressions, such that positive and negative events cancel out. However, their facial behaviour is quite different. The difference is captured by the engagement measure (which would be low for the former child and high for the latter).

*Overall measure for non-verbal enjoyment/engagement (facial expression)*: Enjoyment and engagement will be added to give a single primary measure for non-verbal enjoyment/engagement.

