### Primary measures

‘Curiosity and confidence’ are operationalised in terms of the following observable proxy behaviours.Willingness to taste novel and familiar vegetables, legumes and fruit (supervised self-report)Non-verbal ‘Enjoyment and Engagement’ (from observation of children’s facial expressions)Verbal engagement (child’s speaking time and sensory vocabulary during the activity)Normalised linear combination (mean) of 1, 2 and 3 as an overall measure of ‘curiosity and confidence’ in tasting

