### Willingness-to-taste (WTT)

Children are offered nine plant foods (see Additional file 1: Appendix 1 for list of foods), in a compartmentalised tray. ‘Self-reported WTT’ is simply the proportion of these that a child tastes, as indicated by the faces they draw on their My Tasting Card (see Fig. 2).

Children are instructed that nibbling and licking are included as tasting. A child who eats all of every sample therefore has the same self-reported WTT score as a child who takes tiny nibbles of all samples, though their behaviours are notably different. To finesse WTT scores such that these differences are noted, the human observers coding the video footage will also produce a ‘Gusto’ rating to summarise how enthusiastically each child tastes/eats the food samples, rating from 1 (very unenthusiastic) to 5 (very enthusiastic). These Gusto ratings will be used to weight the self-reported WTT scores (i.e. WTT = self-report WTT * Gusto). We will report both self-report WTT and WTT.

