### Statistical methods

#### Statistical methods for primary and secondary outcomes {20a}

For each participant, pre/post-intervention difference will be calculated for each primary measure, plus the normalised sum of primary measures (to represent overall ‘curiosity and confidence’). Each set of data will be analysed using regression models with pre-post difference as the outcome. Secondary measures will be examined using the same methods as primary measures. The number of clusters is too small to analyse using a multi-level model, however school and class will be included as a covariate.

For each participant, data will be collected at baseline and follow-up. The main outcomes (dependent variables) will be individual scores in WTT, enjoyment/engagement (from facial expression), and verbal engagement at follow-up. The difference in scores between the intervention and the control group will be calculated for each of the primary measures, plus an overall score consisting of the sum of primary measures which represents overall curiosity and confidence. Each set of data will be analysed using two level regression models (where appropriate), to take into account the clustering of children within schools. The analysis will be adjusted for baseline scores.

The intervention should benefit those children most in need of support. To reflect this in our analysis, we will split the participants into three sub-groups according to their score on a given measure at baseline (low, mid, high). Each grouping will cover 1/3 of the range for that measure. It is important that any benefits be observed in the low and/or mid groups and not just be driven primarily by the high group. High scores are considered desirable in all measures.

The liking secondary measure will be examined using the same regression methods.

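### The facial-expression primary measure adds two unscaled scores, so an unstated time unit sets their weights; the definitions of WTT and the overall score also need reconciling

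*Protocol article*

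**What the plan says.** All references are to the protocol article.

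- **Facial expression.** Under *Enjoyment and engagement—facial expression analysis*, coders rate valence from -2 to +2 over the session. Enjoyment is its mean over timesteps. For Engagement the analysts take the first derivative of valence and "calculate its mean absolute value over the number of timesteps in the video recording". Neither the timestep length nor the unit of the derivative is given. *Why use these two measures?* explains that a child with a steady neutral face and a child whose strong positive and negative expressions cancel could have similar Enjoyment, and that Engagement tells them apart. The rule that follows is: "Enjoyment and engagement will be added to give a single primary measure for non-verbal enjoyment/engagement". No scaling is stated.
- **Willingness to taste (WTT).** The first *Primary measures* list, under *Outcomes {12}*, labels this measure as supervised self-report. Under *Willingness-to-taste (WTT)*, "Children are offered nine plant foods" and self-reported WTT "is simply the proportion of these that a child tastes". Observers also give a Gusto score, "rating from 1 (very unenthusiastic) to 5 (very enthusiastic", and then: "These Gusto ratings will be used to weight the self-reported WTT scores (i.e. WTT = self-report WTT * Gusto". Both versions are to be reported.
- **Overall score.** The *Primary measures* list has "Normalised linear combination (mean) of 1, 2 and 3 as an overall measure". In *Statistical methods for primary and secondary outcomes {20a}*, the first paragraph speaks of a normalised sum, while the second has "an overall score consisting of the sum of primary measures which represents overall curiosity and confidence", with no mention of normalisation.

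**The concern.** A raw sum gives each part a weight in proportion to its spread. Enjoyment's spread is fixed by the valence scale. Engagement's spread depends on the time unit: the same video yields a small number per frame and a large one per minute. The primary measure can therefore be nearly all Enjoyment or nearly all Engagement, depending on a setting that nobody chose for that purpose. If it is nearly all Enjoyment, an intervention that made children more animated, in both directions, would barely register in the primary measure. Normalising the overall score later does not help, because the sum has already been formed.

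The other two points are matters of definition. The label self-report and the product with an observer rating are different variables and can order children differently. The overall score is described in three ways. Each choice changes which number is tested.

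**Working it through.** **Inputs from the article.** Valence -2 to +2; nine foods; Gusto 1 to 5; sessions typically 8 to 12 minutes (*Plans for assessment and collection of outcomes {18a}*).

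**Assumptions, not in the article.** A 10-minute (600 s) session; 20 to 120 one-point valence changes; Enjoyment SD 0.2 to 0.5; Engagement SD equal to 50% of its mean; the two uncorrelated.

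**The article's own computed figure.** *Sample size {14}* gives 160 per arm for a difference of 0.5 foods, SD 1.38 and 90% power. Assuming two-sided 5%: 2 × (1.38 × (1.960 + 1.282) / 0.5)² = 160.08, and power at 160 is 89.99%. The figure reproduces and is not in dispute. It rests on the number of foods tried, not on any of the combined scores below.

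**Step 1: size of Engagement.** Engagement = total absolute valence change ÷ number of time units.

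| Changes in 600 s | Per 1-s step | Per 1/25-s step | Per minute |
|---|---|---|---|
| 20 | 0.033 | 0.0013 | 2 |
| 40 | 0.067 | 0.0027 | 4 |
| 120 | 0.20 | 0.008 | 12 |

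**Step 2: share of variance in the raw sum.** Share = s²(Engagement) ÷ [s²(Engagement) + s²(Enjoyment)].

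- 40 changes, 1-s step: s = 0.0333. With Enjoyment SD 0.2, 0.00111 / 0.04111 = 2.7%; with SD 0.5, 0.00111 / 0.25111 = 0.4%.
- 40 changes, 1/25-s step: s = 0.00133; the share is below 0.01% throughout.
- 120 changes, 1-s step: s = 0.1; 0.01 / 0.05 = 20% with SD 0.2, and 0.01 / 0.26 = 3.8% with SD 0.5.
- 20 changes, 1-s step: 0.1% (SD 0.5) to 0.7% (SD 0.2).
- 40 changes, per minute: s = 2; 4 / 4.04 = 99% with SD 0.2, and 4 / 4.25 = 94% with SD 0.5.

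**Step 3: the article's own contrast.** Take a strongly swinging child: 18 ten-second episodes in 600 s, alternating +2 and -2. Enjoyment = (9 × 10 × 2 - 9 × 10 × 2) / 600 = 0. Total change = 18 × (2 + 2) = 72, so Engagement = 72 / 600 = 0.12 at 1-s steps and 72 / 15,000 = 0.0048 at 1/25-s steps. The steadily neutral child scores 0. The gap of 0.12 is 0.24 to 0.6 of the assumed Enjoyment SD, even for this extreme child; at 1/25-s steps it is at most 0.0048 / 0.2 = 0.024 of an SD. At 1-s steps, a child who is neutral apart from one mild smile (+1) of 70 s scores 70/600 + 2/600 = 0.12, the same as the swinging child.

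**Step 4: after standardising.** Changing the time unit multiplies Engagement's mean and SD by the same constant, so its standardised value does not move (provided that no changes are lost within a step). Each part then supplies 50% of the variance when the two are uncorrelated.

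**Step 5: WTT.** Product = foods/9 × Gusto, with range 0 to 5.

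- 2 foods, Gusto 5: 2/9 × 5 = 1.11, against 9 foods, Gusto 1: 9/9 × 1 = 1.00.
- 4 foods, Gusto 5: 2.22, against 9 foods, Gusto 2: 2.00.
- 6 foods, Gusto 5: 3.33, against 9 foods, Gusto 3: 3.00.

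On self-report alone the first pair is 0.22 against 1.00. The version also matters for the baseline subgroups in {20a}, which are thirds of the range. If that means the possible range, a child who tastes all nine foods at Gusto 1 is in the low third on the product (1.00 is below 5/3 = 1.67) and in the top third on self-report.

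**The case against.** The article gives neither timestep nor derivative unit and refers to an appendix, not shown, for the coding regime. A reader might infer that Engagement has almost no weight, full stop. The article does not support that: the share runs from 0.1% to 20% at 1-s steps over 20 to 120 changes, and Engagement dominates if expressed per minute. This part of the objection stands. It does not rescue the sum, because the rule to add without scaling is stated in the article itself, and the appendix is cited for coding, not for combination. Enjoyment and Engagement are also defined and compared separately in the FaceReader validation, so animation is not lost from the data. It may still be lost from the primary measure.

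A reader might also infer that the overall score is a raw sum in which WTT (0 to 5) swamps speaking time (0 to 1). Two of the three statements call it normalised, so this is an inconsistency of wording and not a settled raw sum.

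Finally, weighting by Gusto is deliberate and explained, and both versions will be reported, so an effect on the number of foods tasted would still be visible. In the pilots about 77% of children tasted 7 to 9 of the nine samples without any intervention, so the unweighted proportion sits near its ceiling; making it primary is a trade-off, not an obvious correction. That stands. What remains is that the stated reason concerns children who taste equal numbers, whereas the product also reorders children who taste different numbers, and that the article does not settle which version is the primary measure.

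**Conclusion.** The concern holds in a limited form. Adding Enjoyment and Engagement as raw scores leaves their relative weight to an arbitrary time unit. On the most natural reading, differencing per timestep, Engagement usually contributes little: about 0.4-2.7% of variance with 40 changes at 1-s steps, below 0.01% at 1/25-s steps, and up to 20% with 120 changes at 1-s steps. The sum can then fail to make the distinction for which the second measure was introduced. These percentages rest on the assumed session length, change counts and SDs; the dependence on the time unit does not.

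The WTT reversal (1.11 against 1.00) is exact and needs no assumption, but its consequence is limited to a definition that must be settled. The overall score is likewise a contradiction to reconcile. None of this affects the sample-size figure.

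**What to change.** 1. Standardise Enjoyment and Engagement, each with its pooled baseline mean and SD applied at both time points, and average the two to form the non-verbal primary measure. State the timestep and derivative unit as well.
2. State which WTT version, self-report or the product with Gusto, is the primary measure and enters the overall score, and make the *Primary measures* list agree with the *Willingness-to-taste (WTT)* section. The choice should weigh the near-ceiling pilot counts against the reordering that the product produces.
3. Define the overall score once, as the mean of the standardised primary measures, and use that definition in both paragraphs of {20a}.

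The cost is a few sentences and a few lines of code, settled before the class allocations are released to the lead researcher. No new data are needed, since every component is already collected. The small downside is that scores are in SD units and not raw units; the raw components can be reported beside them.

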### Verbal engagement

Each time step of the video footage is annotated using one of 2 categories/levels of verbal behaviour: 0 = not talking; 1 = talking. These scores will then be summed across time steps, and divided by number of timesteps, to give one number describing the proportion of speaking time across the session. See Additional file 1: Appendix 2 for more details of the video coding scheme.

### Sensory vocabulary

Coders will note (with a key press) each relevant sensory word uttered by the child being observed on video. The sensory vocabulary measure is then total number of relevant sensory words across one ‘Flavour Explorers’ session, normalised by session length.

### Exploratory analysis

#### Liking for the food samples (this is an exploratory analysis)

During the Flavour Explorers tasting activity, the children draw ‘emoji style’ faces to indicate their liking for the food samples they taste (see the “Plans for assessment and collection of outcomes {18a}” section for more details). The primary purposes of this are (a) to serve as supervised self-report of willingness-to-taste and (b) to give the data collection scenario the feel of an ‘activity’, rather than the feel of a ‘test’.

The children have quite a lot of freedom in the faces they draw, and some children (especially the younger ones) are still mastering use of a pen. In pilots, the faces children drew were not always decipherable. As a result, the liking measure is likely to be rather noisy, with limited coverage, especially for children in reception class (i.e. the youngest children). There is no particular reason to anticipate significant pre-post changes in liking. Nonetheless, given we will have some data on children’s liking for the samples, it makes sense to explore this data, noisy as it may be. For these reasons, we will examine Liking as a secondary measure, and an exploratory analysis.

Liking will be calculated as the sum of all the faces drawn on a child’s My Tasting Card, where each face type is rated as follows:‘frowny’ face = 0‘flat’ face = 1‘smiley’ face = 2

Liking will use the same statistical analysis used for the primary measures (see the “Statistical methods for primary and secondary outcomes {20a}” and “Methods for additional analyses (e.g. subgroup analyses) {20b}” sections). We will also calculate correlation between liking and WTT, as we are interested in the extent to which WTT depends on like/dislike for the foods offered.

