**Fig. 2 Fig2:**
[figure not shown]
**a** Each child has a selection of FV in a compartmentalised tray. Children are free to taste (or not) any of the items, in any order. **b** Children record their tasting with an ‘emoji’ drawing to indicate like/neutral/dislike. Untasted items are left blank (e.g. blue circle). The testing table. Up to 4 chidlren participate together, each with their own tray of food samples. Located centrally on the table is a dedicated camera for each child

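### Liking is an undivided sum of face scores, so it rises on average with the number of foods tasted, and its planned correlation with WTT is partly built in

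*Protocol article*

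**What the plan says.** All of this is in the protocol article.

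- **Score.** Under Liking for the food samples: "Liking will be calculated as the sum of all the faces drawn" by the child on the tasting card. The values are "frowny’ face = 0‘flat’ face = 1‘smiley’ face = 2".
- **Untasted foods.** Fig. 2 caption: "Untasted items are left blank".
- **Self-report WTT.** Under Willingness-to-taste (WTT), this "is simply the proportion of these that a child tastes, as indicated by the faces they draw on their My Tasting Card". Nine foods are offered.
- **Weighted WTT.** The same section then defines "WTT = self-report WTT * Gusto", with Gusto rated by video coders from 1 to 5, and says both versions will be reported.
- **Use of Liking.** It gets the same regression as the primary measures. In addition, "We will also calculate correlation between liking and WTT"; the stated purpose is to learn how far tasting depends on whether the child likes the foods. The text does not say which of the two WTT versions is meant.
- **Status.** Liking is called secondary and exploratory. The section expects it to be noisy because some drawings cannot be read, mostly in the youngest children, and foresees no particular pre-post change.

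Nothing in the article divides Liking by the number of foods tasted or otherwise separates the two.

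**The concern.** Liking and self-report WTT come from the same marks on the same card. One counts the faces, and the other adds up their values. The count is the number of terms in the sum.

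Two consequences follow.

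1. **The correlation.** It is meant to show whether willingness to taste depends on liking. If it is positive when there is no such dependence, a reader cannot tell how much of the reported value is informative.
2. **The arm comparison.** The programme aims to make children more willing to explore foods. If it succeeds and liking per food stays the same, the summed score is still expected to be higher in the intervention arm. That could be reported as an effect on liking.

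The section's warning about noise does not cover this. Unreadable drawings are a measurement problem, whereas the coupling to the number tasted has a direction.

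**Working it through.** The protocol gives no figure for Liking or for its correlation with WTT, so there is none to reproduce.

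**Inputs from the protocol**
- Face values 0, 1, 2; blanks add nothing; nine foods.
- Pilot bands (Behaviour patterns expected, based on pilots): about 77% tasted 7–9 foods, about 20% tasted 1–6 and about 2% tasted none. These sum to 99% and are rescaled to 100%.

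**Assumptions, not in the protocol**
- Mix of faces: varied.
- Number tasted: uniform within each pilot band (variants below).
- Gusto: uniform on 1–5 and independent of everything else.
- Null case: face values independent of the number tasted.

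**Step 1: boundary cases.** A child who tastes all nine foods and frowns at each scores 9 × 0 = 0. A child who tastes none also scores 0. With T foods tasted, the maximum is 2T.

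**Step 2: expectation.** Let m be the mean face value per tasted food. Then E[L | T] = mT. With equal thirds of faces, m = 1, so expected Liking is 3 for a child tasting three foods and 9 for a child tasting nine, at identical liking per food. An arm difference of d foods gives an expected difference of m × d in Liking; d = 0.5 and m = 1 give 0.5 with no change in liking.

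**Step 3: distribution of T.**
- E[T] = (0.77 × 8 + 0.20 × 3.5) / 0.99 = 6.93
- E[T²] = (0.77 × 64.67 + 0.20 × 15.17) / 0.99 = 53.36
- Var(T) = 53.36 − 48.01 = 5.35; SD = 2.31

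**Step 4: null correlation with self-report WTT (= T/9).** Cov(L, T) = m·Var(T), which is positive whenever m > 0 and T varies. With v the variance of a single face value,

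r = m·SD(T) / √(E[T]·v + m²·Var(T)).

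For equal thirds (m = 1, v = 2/3): 2.31 / √(4.62 + 5.35) = 0.73.

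**Step 5: null correlation with weighted WTT.** Gusto has mean 3 and mean square 11.
- Var(T × Gusto) = 53.36 × 11 − 48.01 × 9 ≈ 154.8; SD ≈ 12.4
- Correlation of T with T × Gusto = 3 × 5.35 / (2.31 × 12.4) ≈ 0.56
- Equal thirds: 0.73 × 0.56 ≈ 0.41

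**Step 6: other face mixes.** A simulation of 1,000,000 children, with T uniform within the pilot bands, gave:

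| Faces | m | r, self-report WTT | r, weighted WTT |
|---|---|---|---|
| Equal thirds | 1.0 | 0.73 | 0.41 |
| 60% smiles, 20% flat, 20% frowns | 1.4 | 0.84 | 0.47 |
| 60% frowns, 20% flat, 20% smiles | 0.6 | 0.55 | 0.31 |
| 90% frowns, 5% flat, 5% smiles | 0.15 | 0.27 | 0.15 |
| Children differ widely in liking, unrelated to T | – | 0.55 | 0.31 |

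Two variants of T were also run: the top band all at nine foods, and the middle band confined to 4–6. Over all scenarios the range is 0.20–0.85 for self-report WTT and 0.09–0.48 for weighted WTT. These are the scenarios run, not bounds.

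**Step 7: the alternative score.** With Liking as the mean face value per tasted food, among children who tasted at least one, the null correlation with either WTT is within ±0.005 of zero in every scenario.

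**The case against.** **Liking is exploratory.** It does not enter the primary measures or the overall score, and the protocol already warns that it is noisy. The cards keep the individual faces, so a mean can be computed at any time. This stands, and it sets the severity. It does not make the planned correlation interpretable.

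**The effect may be modest for WTT as the protocol names it.** The plain name WTT is given to the Gusto-weighted score, for which the same null gives about 0.41, not 0.73. The pilot also found that children often enjoyed disliking foods, so frown-heavy cards, which lower the figure, cannot be ruled out. In addition, about 77% tasted 7–9 foods, so for most children the number of terms varies little. All of this stands. A reader might infer that the reported correlation is bound to be large, and the documents do not support that.

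**A sum is a legitimate quantity.** The outcomes list describes the construct as liking for the range of foods offered, and a total over the nine is one reading of that. A mean over self-chosen foods has its own bias. A child who tastes six foods and smiles at all has sum 12 and mean 2.0. If the child later adds two disliked foods, the sum stays at 12 and the mean falls to 12/8 = 1.5, although the child has only become more adventurous. This is fair, and it is why the sum need not be discarded in the arm comparison. It does not rescue the sum for the correlation.

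**Blanks and unreadable faces.** A reader might infer that the protocol scores a blank as 0, or that an unreadable face counts as 0. It states neither. The tie between a blank and a frown follows from adding only drawn faces, and the article does not say how unreadable faces are handled.

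**Conclusion.** The point holds as a minor one. On the stated scoring rule, Liking is mechanically coupled to the number of foods tasted. A further food never lowers the score: it adds nothing if the face is a frown and raises it otherwise, so the rise is on average and not for every child. The planned correlation with WTT is therefore positive when liking and tasting are unrelated, and a difference between arms in Liking can come from tasting alone.

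That the built-in component is positive needs only faces unrelated to tasting, some variation in the number tasted, a mean face value above zero and, for weighted WTT, Gusto unrelated to the rest. Its size needs the assumed face mix and spread of counts, and the assumed distribution of Gusto. The ranges in the working should be quoted separately for each WTT version, not as a single value.

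A reader might go further and treat the whole observed correlation as artefact, or take the problem to affect the trial's primary results. Neither follows. A real association may add to the built-in part, and the primary measures do not use the face values.

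**What to change.** 1. For the correlation with WTT, define Liking as the mean face value over foods that were tasted and have a readable face, undefined for a child with none.
2. State whether the correlation is with self-report WTT, Gusto-weighted WTT or both.
3. In the arm comparison, report this mean alongside the sum, and describe the sum as total liking that includes the amount tasted.

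**Cost.** One line of scoring and one extra row of results, with no new data. About 2% of children, going by the pilot, would have no mean because they tasted nothing; any child whose faces are all unreadable would also have none. The mean is conditional on the foods each child chose to taste, so it can fall when a child tries more disliked foods, and it answers only in part whether tasting depends on liking. The report should say so.
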